### Randomisation

Participants will be randomly allocated in a 1:1 ratio to either intervention or control group arms. Randomisation will be stratified by investigator site and baseline pro-brain natriuretic peptide (NT pro-BNP) levels (≤2000, >2000 pg/mL) using minimisation to facilitate balance between the two treatment arms. Randomisation numbers will be computer generated and assigned in strict sequence. At the point of randomisation, participants will be assigned the next randomisation number in the sequence. To maintain concealment and minimise selection bias, randomisation will be performed after the baseline visit by a member of Peninsula Clinical Trials Unit (CTU), independent from investigator teams, using a secure, web-based randomisation system.

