### Trial data collection

Trial data are collected from participants during three clinic visits (at baseline, 4 and 12 months) and by postal questionnaire at 6 months. To encourage participant retention and completeness of data, participants may claim travel expenses associated with clinic visits and are provided with postage-paid envelopes to return questionnaires by post. Furthermore, visits may be partially conducted at participants’ homes if mutually convenient for the research nurse and participant. Participants who are unwilling or unable to travel to research assessments or accommodate home visits are excluded at the point of consent.

At the baseline clinic visit, after written informed consent has been obtained by the research nurse, the following information will be collected:
Medical history (including comorbidities (number and severity scored with Charlson Co-morbidity Index), New York Heart Association class, HF aetiology, concomitant HF medication and presence of implantable HF devices);Healthcare resource utilisation over the prior 6 months;Sociodemographic information (ie, date of birth, ethnicity, height, weight, employment status, education level, smoking status).

Participating patients will be asked to:
Complete a booklet comprising the primary and secondary outcome questionnaires;Perform an the incremental shuttle walk test;Provide a (∼4 mL) blood sample for measurement of NT pro-BNP levels;Wear a wrist-worn accelerometer for 7 days.

Participating caregivers will also be asked to provide sociodemographic information (ie, date of birth, ethnicity, weight, employment status, education level and smoking status) and to complete a booklet comprising their outcome questionnaires.

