### Data analysis

#### Primary and secondary outcomes

All analyses, quantitative and qualitative, will be conducted according to best practise and reported in accordance with Consolidated Standards of Reporting Trials (CONSORT) guidelines for reporting of clinical trials^31^ and appropriate guidelines for reporting process evaluations^32^ and qualitative research.^33^ Baseline sociodemographic and health-related variables will be reported descriptively by treatment arm, in order to assess whether the inferential analyses require adjustment for any unbalanced variables.

The primary analyses for all patient and caregiver outcomes will be based on a between-group, intention-to-treat, complete case approach, using data collected at 12 months’ follow-up. The outcomes will be analysed using the regression method appropriate to the data, that is, linear regression modelling for continuous outcomes, survival analysis based on the Cox proportional hazards regression model for time-to-event data, and Tobit regression analysis for EQ-5D-5L. All analyses will adjust for baseline score of the outcome variable (where applicable), as well as minimisation variables previously described, and sociodemographic and health-related variables that are found to be unbalanced at baseline.

Secondary analyses will be undertaken on patient and caregiver outcomes as repeated measures analysis using all follow-up assessment points (4, 6 and 12 months). In addition, a per protocol analysis of the primary outcome will be performed using 12-month follow-up data. A per protocol definition (based on a minimum level of intervention uptake and adherence deemed necessary to achieve improvement in outcomes) will be agreed prior to the start of data analysis. If there is more than 5% loss to follow-up for the primary outcome at 12 months, multiple imputation methods will be used as a sensitivity analysis to address the issue of missing data. The following subgroups will be assessed: the stratification variables of trial centre and severity of HF (NT pro-BNP levels), plus time since HF diagnosis and the inclusion (or not) of a caregiver.

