The potential for differential intervention effects within patient subgroups (ie, moderation by patient characteristics) will be explored using interactions within linear regression modelling for the primary outcome only. Mediation analyses will be used to assess the extent to which secondary outcomes at intermediate follow-up (eg, self-efficacy or physical activity levels at 4 months) or progress tracker self-care behaviours (eg, self-reported exercise, stress or anxiety management activities) can explain between-group differences in the primary outcome at 12 months. Moderation and mediation analyses will be exploratory in nature as no formal power calculation for interaction effects has been performed.

Serious adverse events will be presented descriptively by treatment arm.

All between group outcome results will be presented as means and 95% CIs. No correction of p values for multiplicity of testing will be undertaken. However, the primary outcome (MLHFQ at 12 months) analysis will be performed before all other analyses and the p values of all subsequent analyses interpreted in the context of multiple testing. No interim analyses will be performed. All analyses will be conducted by a statistician who is blinded to treatment arm, using Stata V.12.

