#### Economic outcomes

Means (and SDs) for resource use and costs will be presented for baseline assessment, and for resource use over the 12-month follow-up period. Regression methods will be used to estimate mean costs per group and to compare mean costs between treatment and control groups. MLHFQ data will be drawn from the main statistical analyses. QALY data will be derived from trial data on EQ-5D-5L, using a UK algorithm/tariff, in the first instance those derived from Dolan^34^ (via van-Hout *et al*^35^; although it is expected that a UK tariff will be published at the time of analysis), for the 5-level EQ-5D). Derived health state values will be used to estimate QALYs through application of standard area-under-the-curve methods^36^ using all data from baseline to 12-month. Analysis of mean QALY per group, and differences between groups will be undertaken using regression based methods, adjusting for baseline EQ-5D-5L, and using covariates as the main statistical analyses on effectiveness. As analyses are over a 12-month period no discounting of (future) costs or outcomes is required.

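### The fixed core of the primary model is sound, but its additional covariates are chosen by observed baseline imbalance and not by prognostic value

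*Protocol article*

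**What the plan says.** Under Data analysis, Primary and secondary outcomes, the article says that baseline variables are tabulated by arm "in order to assess whether the inferential analyses require adjustment for any unbalanced variables". The model rule follows: "All analyses will adjust for baseline score of the outcome variable (where applicable), as well as minimisation variables previously described", and then a third group of covariates, "and sociodemographic and health-related variables that are found to be unbalanced at baseline".

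The minimisation variables come from the Randomisation section: "Randomisation will be stratified by investigator site and baseline pro-brain natriuretic peptide (NT pro-BNP) levels", with NT pro-BNP cut at 2000 pg/mL.

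The pool for the third group is in Trial data collection. It holds "Sociodemographic information (ie, date of birth, ethnicity, height, weight, employment status, education level, smoking status" and, from the medical history, the Charlson index with "New York Heart Association class, HF aetiology, concomitant HF medication and presence of implantable HF devices".

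The Economic outcomes section adjusts the QALY analysis for baseline EQ-5D-5L, "using covariates as the main statistical analyses on effectiveness", so the same selection reaches the economic result. Nowhere does the article make a model with only the fixed covariates the primary one.

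**The concern.** The first two groups of covariates are settled before any data exist. The third is settled by looking at the trial's own data by arm. Allocation is made by the trials unit after the baseline visit through a web-based system, so any remaining difference in, say, education level or height is chance. Such a difference does not tell us whether the variable predicts MLHFQ at 12 months, and that is what decides whether adjusting for it helps. Imbalance is thus the wrong selection criterion, and an agreed numerical cut-off would not make it the right one.

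Three things follow for the confirmatory analysis:

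- The covariate set would differ between hypothetical repeats of the same trial for reasons unrelated to the outcome.
- A strong predictor that happens to be balanced is left out, and the precision it would have given is lost.
- Adjusting only when imbalance is seen makes the model standard error differ from the actual variability of the estimate.

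The same text requires the per protocol definition to be agreed before data analysis starts. It gives no matching commitment for the covariates of the primary model.

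**Working it through.** **1. The plan's own figure.** The Sample size section gives a 5-point difference, SD 10, type I error 0.05 (taken as two-sided) and 90% power.

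- n per group = 2 × (1.960 + 1.282)² × 10² / 5² = 84.1, rounded up to 85. This matches the stated 85.
- With 20% attrition, 85 / 0.80 = 106.25, rounded up to 107, against 108 stated.

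The calculation uses an unadjusted SD, so the choice of covariates does not alter it.

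**2. Size of the pool.** Trial data collection names seven sociodemographic variables (date of birth, ethnicity, height, weight, employment, education, smoking) and five health-related ones (Charlson index, NYHA class, aetiology, HF medication, devices): 7 + 5 = 12.

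**3. Chance that at least one covariate is added.** The article states no test or threshold. As an illustration, assume k independent variables, each flagged when p < a. The chance is 1 − (1 − a)^k and the expected number flagged is k × a.

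| k | a | Chance of at least one | Expected number |
|---|---|---|---|
| 12 | 0.05 | 1 − 0.95^12 = 46% | 0.6 |
| 12 | 0.10 | 1 − 0.90^12 = 72% | 1.2 |
| 12 | 0.20 | 1 − 0.80^12 = 93% | 2.4 |
| 6 | 0.05 | 1 − 0.95^6 = 27% | 0.3 |
| 20 | 0.05 | 1 − 0.95^20 = 64% | 1.0 |

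**4. What adding covariates does to the result.** This was simulated with 86 complete cases per arm (108 × 0.80 = 86.4) and 4000 runs per setting. The assumptions are not in the documents: outcome SD 10, correlation 0.6 between baseline and 12-month score, and 12 independent covariates that together explain 10% or 30% of outcome variance. Site, NT pro-BNP and minimisation were not modelled. Four rules were compared: no extra covariates, or adding those flagged at p < 0.05, 0.10 or 0.20.

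- *Type I error, one threshold applied mechanically:* 2.6% to 5.0%, so at or below nominal.
- *Calibration:* the average model standard error exceeds the actual SD of the estimate in every threshold setting. The smallest gap is 1.230 against 1.211 (1.230 / 1.211 = 1.02), with threshold 0.05 and 10% of variance explained. The largest is 1.190 against 1.043 (1.190 / 1.043 = 1.14), with threshold 0.20 and 30% explained. The stated standard error is thus about 2% to 14% too large.
- *Spread of the estimate across the four rules:* median 0.4 to 0.6 points, 95th percentile 1.0 to 1.5 points, against the 5-point target.
- *Runs in which significance at 0.05 depends on the rule:* 4% to 6% with no effect, 12% to 20% at a true 3-point difference, 1% to 2% at 5 points.
- *Picking the most favourable of the four rules:* type I error 6.5% to 7.1%. The article plans nothing of the kind.
- *All 12 covariates fixed in advance:* type I error 4.8% to 4.9%. Power at a 3-point difference is 72% to 90%, against 68% to 73% for the threshold rules. This is a favourable case, because every covariate in the fixed set is truly prognostic.

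**The case against.** Much can be said for the plan, and most of it stands.

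- **Most of the primary analysis is fixed.** Outcome, time point, regression type, intention-to-treat complete-case set, baseline score, site and NT pro-BNP are all named. A reader might infer that the primary analysis as a whole is chosen from the data. The text does not support that, because only the supplementary covariates are open.
- **Safeguards exist.** Selection uses baseline variables, not outcomes. The article also says "All analyses will be conducted by a statistician who is blinded to treatment arm", and the primary analysis is run before the others. This makes it hard to steer the result. It does not settle the covariate set, since imbalance between coded arms is visible without knowing which arm is which.
- **The definition of imbalance may be elsewhere.** A threshold and candidate list are details that an article can leave to the full protocol or SAP, so their absence is not counted here. With a pre-set threshold, two analysts would reach the same model, and the simulated differences between rules would largely fall away. The criterion would still be chance imbalance.
- **The 46% and 72% rest on assumptions.** The article speaks of descriptive reporting, not significance tests, and some variables (height and weight, for example) are probably correlated.
- **The precision loss is bounded.** The baseline score, site and NT pro-BNP are already in the model. Any further gain depends on how prognostic the extra variables are, which the documents do not say.

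**Conclusion.** The point holds for the additional covariates, and it concerns a rule that the article states, not a detail left out. Chance imbalance, not prognostic value, completes the primary model, the other patient and caregiver models and, through them, the QALY model. Serious adverse events are only described and are not affected.

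The size is moderate. With 12 independent variables and an assumed screen at p < 0.05 or p < 0.10, at least one covariate would be added by chance in 46% or 72% of repeats. A reader might take these as the chance that the conclusion changes, which they are not. Under the simulation's assumptions, the significance verdict depends on the rule in 1% to 2% of trials at the 5-point target, though in 12% to 20% at a true 3-point difference.

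A reader might also infer a raised false-positive risk. That is not supported: one rule applied mechanically is at or below the nominal level. The harm is an incompletely pre-specified primary model, a standard error that tends to be somewhat too large, and precision forgone. The sample size is unaffected. Severity: should fix.

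**What to change.** In Data analysis, Primary and secondary outcomes:

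- Delete the clause that adds variables found to be unbalanced, and the matching purpose given for the baseline table. The table is then for description only.
- State that the primary and secondary models adjust for the baseline value of the outcome (where there is one), site and NT pro-BNP, plus any prognostic covariates named before the data are seen by arm. NYHA class and age are possible candidates, as both can be taken from data already collected.
- If adjustment for chance-unbalanced variables is still wanted, report it as a labelled sensitivity analysis, with its selection rule set beforehand.

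The QALY analysis needs no separate change, because it takes its covariates from the main analyses. The cost is a sentence or two in the protocol and SAP, with no new data and no change to the 85 evaluable or 108 recruited patients per group.

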## Aims and hypothesis

This trial aims to assess the clinical effectiveness and cost-effectiveness of the addition of the REACH-HF intervention to usual care in patients with systolic HF and their caregivers. The primary hypothesis is that REACH-HF plus usual care (as received by participants in the ‘intervention group’) compared with usual care alone (as received by participants in the ‘control group’) can improve the disease specific HRQoL of patients at 12 months’ follow-up (primary outcome). Secondary objectives of the trial are:
To compare secondary outcomes between patients in the intervention and control group (comprising the composite outcome of all-cause death or HF-related hospital admission, brain natriuretic peptide levels, exercise capacity, psychological well-being, level of physical activity, generic health-related quality of life and safety);To estimate the cost-effectiveness of the REACH-HF intervention plus usual care versus usual care alone, for patients with systolic HF;To explore the moderators and mediators of change in disease-specific HRQoL of patients in intervention and control groups;To assess the impact of, acceptability and satisfaction of the REACH-HF intervention to patients and caregivers;To compare psychological well-being, quality of life, self-care activities, and burden, between caregivers in the intervention and control groups;To check the fidelity of delivery of the REACH-HF intervention to patients and caregivers.

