### Sample size

The sample size is based on an effect size that represents a clinically important difference and is plausible. The developers of the MLHFQ have determined that five points is the minimal clinically important difference in score.^15^ With a type I error of 0.05 and power of 90%, 85 patients per group are required to detect a five-point difference in the MLHFQ score, assuming a SD of 10.^25^ With an attrition rate of 20% (in accordance with the level of attrition seen in previous trials),^26^
^27^ 108 patients are required per group. The plausibility of this between group difference is supported by the Cochrane review of CR in HF, which reported a mean pooled between group difference of 10.3 (95% CI 4.8 to 15.9) points in MLHFQ score.^28^ The proposed sample size is likely to be conservative given the analysis of covariance approach to primary outcome analysis and adequate to detect an important difference in a number of secondary outcomes, including the ISWT (50 m) and Hospital Anxiety and Depression Scale (1.5 points) at a power of 80% or higher.

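### Moderation by heart failure severity appears to be tested with NT-proBNP cut at 2000 pg/mL, although a numeric baseline value exists for every randomised patient and the exploratory interaction test needs no cut

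*Protocol article*

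**What the plan says.** Under Randomisation, the protocol article minimises on site and on "baseline pro-brain natriuretic peptide (NT pro-BNP) levels (≤2000, >2000 pg/mL". This is the only place where a form is given for NT-proBNP as a stratification variable.

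Under Data analysis, Primary and secondary outcomes, all analyses adjust for the minimisation variables as already described. The subgroups include "the stratification variables of trial centre and severity of HF (NT pro-BNP levels", plus time since diagnosis and presence of a caregiver. Subgroup effects are treated as moderation and tested by interactions in linear regression, for the primary outcome only. The section calls this exploratory because "no formal power calculation for interaction effects has been performed".

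Moderation is nevertheless a listed secondary objective under Aims and hypothesis: "To explore the moderators and mediators of change in disease-specific HRQoL of patients in intervention and control groups".

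The blood sample is taken at the baseline visit (Trial data collection). Allocation waits for its result (footnote to Table 1, Outcome measures). A numeric value therefore exists for every randomised patient. The article plans no continuous NT-proBNP term, except as the baseline value when NT-proBNP is itself the outcome.

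**The concern.** Minimisation needs categories; a regression interaction does not. If the moderator is the two-level factor, a patient just above 2000 pg/mL counts the same as the most severe patient, and one just below counts the same as the mildest. Any gradient of treatment effect within each half is lost.

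The stake is limited to one analysis, the test of whether benefit on the MLHFQ varies with severity. That analysis serves a stated objective in a trial not sized for interactions. Discarding information from a measurement already in hand weakens a test that is weak to begin with, and makes the answer depend on a single threshold.

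**Working it through.** **Inputs from the protocol article (Sample size).** "With a type I error of 0.05 and power of 90%, 85 patients per group are required". The target is an MLHFQ difference of 5 points with SD 10. After 20% attrition, "108 patients are required per group". Allocation is 1:1.

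**Reproducing the plan's figure.** Two-sided 0.05, 90% power, difference 5 and SD 10 give 85 per group. Dividing by 0.8 gives 106.25, so 107 against the stated 108, which agrees to within one patient per group. The interaction calculations below use 2 × 85 = 170 completers and SD 10.

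**Assumptions not in the article.** Log NT-proBNP is normal, effect modification is linear on the log scale, and a share p of patients lies above 2000 pg/mL. Because p is not reported, a range is shown. The result is the same for p and 1 − p.

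**Information kept by the cut.** For a normal covariate cut at the point with share p above it, the proportion kept is r = φ(z)² / [p(1 − p)], where φ is the standard normal density at the cut:

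- p = 0.5: 0.3989² / 0.25 = 0.637
- p = 0.3: 0.3477² / 0.21 = 0.576
- p = 0.2: 0.2800² / 0.16 = 0.490

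**Power of the interaction test.** The standard error of the interaction slope per SD of log NT-proBNP is 2 × 10 / √170 = 1.534. The slope detected with 80% power as a continuous term is (1.960 + 0.842) × 1.534 = 4.3 MLHFQ points per SD. With the cut, power is Φ(2.802 × √r − 1.960), and the equivalent sample size is 170 × r. The residual SD is held at 10 for both tests, which slightly favours the cut.

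| Split at 2000 pg/mL | Information lost | Power with cut (continuous 80%) | Equivalent patients of 170 |
|---|---|---|---|
| 50/50 | 36% | 61% | 108 |
| 30/70 | 42% | 57% | 98 |
| 20/80 | 51% | 50% | 83 |

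More uneven splits lose more: 57% at 15/85 and 66% at 10/90.

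**Effect on the adjusted primary comparison.** Assume a partial correlation ρ between log NT-proBNP and the 12-month MLHFQ score. The ratio of treatment standard errors, cut to continuous, is √[(1 − ρ²r) / (1 − ρ²)]. For ρ from 0.1 to 0.3 and the splits above, the standard error rises by 0.2% to 2.5%. With 85 per group, power changes by about 0.1 to 1.2 percentage points (for example, 92.7% against 91.5% at ρ = 0.3 and a 20/80 split).

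**Choice of scale.** For a log-normal variable with log-SD s, a linear term in the raw value captures s² / (exp(s²) − 1) of the log-scale signal: 71% at s = 0.8 and 38% at s = 1.3. An untransformed term may therefore do no better than the cut.

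**The case against.** The strongest reply is that the coding is not stated. The subgroup sentence gives no threshold, and it also lists time since diagnosis without categories, so it may only be naming variables. An analysis plan that is not shown may use a continuous term. This stands as a limit on certainty. It does not remove the point, because calling severity a stratification variable refers back to the one form that the article defines.

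Second, linearity is assumed. If benefit really changes in a step at 2000 pg/mL, the ranking reverses, and under normality the linear term then keeps only the same fraction r. The article supports neither shape over the other, so the loss must be stated as conditional.

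Third, the illustrative interaction is large. At 4.3 points per SD around an average benefit of 5, patients 2 SD apart from the mean would have a benefit of 13.6 points at one end and harm of 3.6 at the other. For an interaction of 2 points per SD, power is about 26% continuous against 18% (50/50) or 15% (20/80), which is inadequate either way. This stands: the change improves the test but does not make it well powered.

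Fourth, the cut is fixed in advance, estimates within stratification levels are conventional and readable, and the plan already labels the analysis exploratory. All true. These are reasons to keep the subgroups for display, but they do not require the cut in the test.

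A reader might also infer that adjusting the outcomes for the two-level factor wastes a third to a half of the information in the main analysis. The documents do not support that. The loss concerns the covariate and not the trial, adjusting for a factor in the form used to allocate is accepted practice, and baseline MLHFQ is already in the model.

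**Conclusion.** The point holds as a low-cost improvement to one exploratory analysis. The two-level severity moderator is the natural reading but an inferred one. The loss of about 36% to 51% of the moderator's information, and the fall from 80% to about 50% to 61% power, rest on approximate log-normality, log-linear modification and a share of 20% to 80% above the cut. The article reports none of these.

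The primary comparison is essentially untouched: at most about 1.2 percentage points of power under the assumed correlations. Its adjustment for the minimisation factor is not an error.

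**What to change.** - Keep the ≤2000/>2000 factor for minimisation and in the adjustment set of every model.
- Prespecify the moderation test for severity as arm by log baseline NT-proBNP, with the main effect of log NT-proBNP in the model. Name the log scale explicitly.
- Report treatment effects in the two NT-proBNP subgroups for display, not as the test.
- Check linearity on the log scale and report the check.
- Optionally, add log NT-proBNP as a covariate in the primary model for a small gain in precision.

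The cost is a sentence or two in the analysis plan, one degree of freedom and the linearity assumption. No new data are needed. If the analysis plan already specifies a continuous term, it is enough to align the wording.
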